**15.2 Background**

### 15.2.1 Circadian Rhythm

Circadian rhythm is controlled by clock genes which cause diurnal variations in proteins CRY, PER, CLOCK and BMAL^[[58]](#footnote-58)^ . Barnett et al, 2014 ^[[59]](#footnote-59)^ showed an association between late radiotherapy toxicity and a SNP (rs13116075) close to the CCRN4L gene (for the protein nocturnin). CCRN4L is a gene controlled by circadian rhythm and is linked to metabolism of lipids ^[[60]](#footnote-60)^. Levels of this protein undergo diurnal variation with peaks at night. It has also been linked to inflammation^[[61]](#footnote-61)^ which may be the possible mechanism for increasing radiotherapy toxicity. Clock genes/proteins then in turn exert effects on other proteins which have a wide physiological effect. This includes DNA damage checkpoints and apoptosis mechanisms which govern repair in normal tissues following radiotherapy. Variations in these clock genes can influence a person’s sleep wake cycle^[[62]](#footnote-62)^ and ability to repair DNA damage^[[63]](#footnote-63)^ .

### 15.2.2 Rationale for the study

We hypothesise that radiotherapy toxicity is affected by variation in clock genes. In turn, timing of radiotherapy would also affect whether patients develop side-effects depending on their clock genotype. Using data already collected from a pilot cohort we have observed a significant increase in late radiotherapy reaction in patients with a particular clock genotype (PER 3 and CCRN4L) when these patients were treated in the mornings. We have also observed that patients in the pilot cohort with a particular chronotype (assessed using the Munich Chronotype questionnaire) correlate with risk of radiotherapy toxicity. This questionnaire has been completed by the pilot cohort and has been used extensively in many other studies. This questionnaire was developed as part of an EU-funded chronobiology grant and has been validated in more than 50,000 volunteers so far.

## 15.3 Sub-study research plan

### 15.3.1 Study objectives and design

The main objective of the Circadian Rhythm REQUITE sub-study is to validate our findings from the pilot study that circadian rhythm can be used to predict a patient’s risk of developing radiotherapy toxicity.

Secondary objectives include establishing if variations in chronotype relate to polymorphisms in circadian rhythm genes. The main part of this sub-study will be questionnaire based.

### 15.3.2 Patient selection and recruitment

All breast and prostate cancer patients recruited to the main REQUITE study at the University of Leicester will be approached to take part in this sub-study. This will give a maximum sample size of 600. However, it is anticipated that there will be a 50% return rate giving 300 participants. It is expected that the sample will include adequate representation of age, ethnicity, disease factors, co-morbidities (e.g. diabetes or anxiety/depression) and degrees of toxicity.

Patients will be consented for the questionnaire sub-study using an additional consent form and additional patient information sheet.

### 15.3.3 Study methodology and data analysis

Selected participants will be sent the Munich chronotype questionnaire to collect information on their sleep wake cycle. A patient invite letter, patient information sheet and consent form will be sent alongside the questionnaire, and patients will be asked to sign and return the consent form along with the completed questionnaire in a pre-paid envelope that is provided. The consent form will be counter-signed on receipt and a copy returned to the patient. Data from the completed questionnaire will be analysed using an algorithm created by the University of Munich to generate chronotype for each participant.

Genotyping for circadian rhythm genes will be undertaken at the University of Leicester using DNA isolated from EDTA blood samples previously collected as part of the REQUITE study (sample A). This will then be correlated with data from the chronotype and radiotherapy toxicity to perform further analysis.

## 15.4 Sub-study research arrangements

### 15.4.1 Compliance and data protection

All investigators and researchers involved with the study must comply with the national requirements for data protection with regard to the collection, storage, processing and disclosure of personal information and agree to uphold the appropriate core principles.

Patient notes and study files at site must be kept in a secure storage area with limited access.

Any access required to the REQUITE database will be strictly limited via usernames and passwords. Published results will not contain any personal data that could allow identification of individual patients.

### 15.4.2 Ethical and regulatory requirements

The study will be conducted in accordance with the approved protocol, the Declaration of Helsinki, ICH Guidelines for Good Clinical Practice (ICH GCP), relevant regulations and standard operating procedures.

Research Ethics approval for this sub-study will be sought from the NRES Committee North West – Greater Manchester East by way of major amendment to the previously approved protocol (ref. 14/NW/0035). Permission to conduct the sub-study will be sought from the R&D department at participating centres.

The local Principal Investigator (PI) must ensure that the study protocol, patient information sheet, consent form, family doctor letter and submitted supporting documents have been approved by the appropriate regulatory bodies and research ethics committee(s) prior to any patient recruitment.

Any agreed substantial amendments must also be submitted and receive ethical and regulatory approval prior to implementation. It is the responsibility of the PI at each site to ensure that the study has all the necessary approvals in place. A site initiation meeting must be completed prior to each study centre opening to recruitment.

Patients will be recruited onto the sub-study using a separate Circadian Rhythm REQUITE sub-study patient information sheet and separate consent form. A patient information sheet will be presented to potential participants detailing the nature of the study, the implications of participating and any potential risks or inconveniences involved in taking part. It will be clearly stated that the participant is free to withdraw from the study at any time, for any reason, without prejudice to future care and with no obligation to give the reason for withdrawal. The participant will be allowed sufficient time (a minimum of 24 hours) to consider the information and decide whether to take part before consent is sought. Written informed consent will then be obtained by means of patient dated signature and dated signature of the person who presented and obtained the informed consent.

Patients wishing to withdraw from the study will not be replaced. If a participant decides to withdraw, their coded blood samples and information will be retained for use within REQUITE and for future medical research unless the patient makes a specific request otherwise. If specifically requested (either verbally or in writing to a member of the research team), the blood samples will be destroyed and the medical information removed from the REQUITE database.

### 15.4.3 Management and oversight arrangements

This sub-study will be overseen by the main REQUITE Study Management Group (SMG), as the patients in this sub-study will come from the main study. The conduct of this sub-study will be monitored as part of the arrangements for the main study.

The University of Manchester will remain as sponsor for this sub-study. The contact point is:

[name]

Associate Vice-President (Research Integrity)

The University of Manchester

[name]

Email: [[contact]](mailto:[contact])

[contact]

The University of Manchester has insurance for research involving human subjects that provides cover for legal liabilities arising from its actions or those of its staff, subject to policy terms and conditions. For participating sites which are part of the NHS, the NHS indemnity scheme will also apply.

# 16.0 SUB-STUDY 4: REQUITE-BP (Breast Pain) Sub-study

## 16.1 Summary

| **TITLE** | REQUITE - Predictors of long-term breast pain after breast cancer treatment |
| --- | --- |
| **STUDY DESIGN** | A study embedded within the REQUITE main study administering pain questionnaires to a sample of breast cancer patients recruited into the main study to evaluate and better understand chronic, long-term breast pain by incorporating pain sensitivity |
| **TARGET DISEASE** | Cancer of the breast |
| **PRIMARY STUDY OBJECTIVE** | To identify clinical and biological factors that are predictive of long-term breast pain |
| **SECONDARY STUDY OBJECTIVE** | To develop a prediction model for long-term breast pain (> 2 years) after breast cancer treatment |
| **PARTICIPATING SITES** | University of Leicester |
| **STUDY POPULATION** | Breast cancer patients recruited into the main REQUITE study |
| **RECRUITMENT TARGET** | Sample size expected to be 50% of REQUITE patient cohort (n=350), approximately 175 patients. |
| **FOLLOW UP VISITS** | Single administration of questionnaires at follow-up visit or by post |
| **STUDY DURATION** | Patients to be recruited during long-term follow-up of the main REQUITE study |
| **SAMPLE COLLECTION** | Pain assessment questionnaires: Pain Sensitivity questionnaire^[[64]](#footnote-64)^, McGill pain questionnaire^[[65]](#footnote-65)^, West Haven-Yale Multi-dimensional Pain Inventory (REF) ^66^, Hospital Anxiety and Depression scale (HADs)^67^ and Pain Catastrophizing scale^68^. |
| **POWER CALCULATIONS** | We expect around 50% of the REQUITE patients to consent to enter this study, giving questionnaire data on 175 patients. In terms of genotyping, this cohort size will allow 80% power at α=0.05 to detect an Odds Ratio >1.42 given realistic parameters (prevalence 0.44, allele frequency 0.2, D’ 0.8) |

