## 12.1 Breast Patients

| **ACTIVITY** | **FORM LABEL** | **TIME POINT** | | | | |
| --- | --- | --- | --- | --- | --- | --- |
|  |  | **Baseline (prior to radiotherapy unless otherwise indicated)^** | **End of radiotherapy*** | **3 months from start of radiotherapy^+^** | **12 months from start of radiotherapy^+^** | **24 months from start of radiotherapy^+^**  ***(1° endpoint)***  ***Also yearly to 60 months*** |
| **Enrolment Form** | B1 | X |  |  |  |  |
| **Consent** | RQ1 | X |  |  |  |  |
| **Blood Collection^** | RQ2 | X^ |  |  |  |  |
| **Patient Factors Form** | B2 | B |  |  | F | F |
| **Clinical and Treatment Data Collection Form** | B3 |  | X |  |  |  |
| **Photographic Assessment Form** | B4 | X |  |  |  | X |
| **Health Professional Toxicity Data Form** | B5 | X | X | X | X | X |
| **EORTC C30** | B6a | X | X | X | X | X |
| **EORTC BR23** | B6b | X | X | X | X | X |
| **MFI** | B6c | X | X | X | X | X |
| **GPAQ** | B6d | X | X | X | X | X |
| **HBIS** | B6e | X | X | X | X | X |
| **Withdrawal Form** | B7 |  |  |  |  | X |
| **Outcome Data Form** | B8 |  |  |  |  | X |

^ Consent and blood collection can either be prior to chemotherapy or radiotherapy (see Section 6.2)

* 1-2 days prior to end of radiotherapy or last day

^+^ Plus/ minus four weeks

X: Same version for every time point

B: Baseline version

F: Follow-up version

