### 16.3.2 Patient selection and recruitment

Patients taking part in the main REQUITE study at the University of Leicester will be contacted with additional pain questionnaires^64-67^ and the Pain Catastrophizing scale^68^ through post or face-to-face contact at follow-up clinics. Patients will be given/ sent a cover letter along with the additional questionnaires. They will be consented for the sub-study using one additional consent form,. If participating by post, consent forms will be countersigned on receipt.

From an original sample size of 350 treated by breast-conserving surgery and adjuvant radiotherapy, we expect a 50% return rate, yielding 175 participants. It is expected that the sample population will be representative of age, ethnicity, presence vs. absence of chemotherapy, presence vs. absence of hormonal therapies, use of painkillers, co-morbidities, and stage of disease.

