### 16.3.3 Study methodology and data analysis

In order to assess patients’ perspective of chronic breast pain we will administer and collect questionnaire data on pain and pain sensitivity either face-to-face in the clinic or by post. We will include five questionnaires (Pain Sensitivity questionnaire^64^, McGill pain questionnaire^65^, West Haven-Yale Multi-dimensional Pain Inventory (REF)^66^, Hospital Anxiety and Depression Scale (HADS)^67^, and the Pain Catastrophizing scale^68^. The inclusion of the Pain Sensitivity^64^ questionnaires is to collect data to account for confounders of pain perception that are not already present in the REQUITE data.

Pain questionnaires will be sent out with a cover letter, consent form and patient information sheet attached. Postal questionnaires will have a pre-paid envelope enclosed to return questionnaires and the consent form. Each questionnaire will be identified using the patient’s unique REQUITE ID so data can be matched with the REQUITE database, but all other aspects are anonymised.

We will investigate the association of long-term breast pain at 2 years recorded in the main study using the EORCTQLQ-C30 and –BR23^102^ tools by integrating the additional questionnaire data with predictive variables from the REQUITE database, including but not limited to treatment details, co-morbidities, toxicity and other PROMs data using multivariate statistical analysis. Whole genome SNP data will be also be incorporated.

^102^ Sprangers MAG, Groenvold M, Arraras JI, et al.. The European Organisation for Research and Treatment of Cancer: Breast Cancer Specific Quality of Life Questionnaire Module: First results from a three-country field study. J. Clin. Oncol

14:2756-2768, 1996.

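### REQUITE-BP claims 80% power for an odds ratio of 1.42 with 175 patients, but its own inputs give about 18–26%

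*Protocol*

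**What the plan says.** Section 16.1 of the Protocol (REQUITE-BP summary, power calculations) expects half of the 350 Leicester breast patients to take part, "giving questionnaire data on 175 patients". For genotyping it then states that "this cohort size will allow 80% power at α=0.05 to detect an Odds Ratio >1.42", "given realistic parameters (prevalence 0.44, allele frequency 0.2, D’ 0.8"). Section 16.3.2 confirms that 175 is the whole sample, cases and non-cases together: "we expect a 50% return rate, yielding 175 participants". The genetic model, the sidedness of the test and the marker frequency are not given.

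Section 16.3.3 takes the outcome from the main study rather than from the new pain forms: "We will investigate the association of long-term breast pain at 2 years recorded in the main study using the EORCTQLQ-C30 and –BR23" tools. It adds: "Whole genome SNP data will be also be incorporated".

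**The concern.** At prevalence 0.44, 175 patients split into about 77 with pain and 98 without. That is a small sample for a common variant with a modest effect, so 80% power at an odds ratio of 1.42 looks too high on sight.

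The primary objective of the sub-study is to identify clinical and biological factors that predict long-term breast pain. If the stated power is accepted, a null SNP result would be read as good evidence against an effect of this size. If the true power is near 20%, such a result says very little. The alpha of 0.05 also suits a single SNP chosen in advance, while the analysis section brings in whole-genome data without saying that the power figure does not carry over.

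**Working it through.** **Inputs from the Protocol.** N = 175 (350 × 0.5; Sections 16.1 and 16.3.2). Prevalence 0.44, allele frequency 0.2, D' 0.8, alpha 0.05, odds ratio 1.42 (Section 16.1).

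**Assumptions where the text is silent.** Two-sided test; per-allele (log-additive) odds ratio; Hardy-Weinberg proportions 0.64 / 0.32 / 0.04; 0.2 is the allele frequency in the whole cohort; marker frequency also 0.2. D' = 1 is shown alongside 0.8 in case the odds ratio is meant at the typed SNP.

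**Step 1, risks by genotype.** Solving for overall prevalence 0.44 with odds ratio 1.42 per allele gives risks of 0.405, 0.492 and 0.579 for 0, 1 and 2 copies.

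**Step 2, allele frequencies.** These risks imply 0.2315 in patients with pain and 0.1753 in those without, a difference of 0.0562. With D' 0.8 the difference at the marker is 0.8 × 0.0562 = 0.0450.

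**Step 3, power at N = 175.** There are 2 × 77 = 154 and 2 × 98 = 196 alleles. SE = √[0.2 × 0.8 × (1/154 + 1/196)] = 0.0431.
- D' = 1: z = 0.0562/0.0431 = 1.31; Φ(1.31 − 1.96) ≈ 0.26.
- D' = 0.8: z = 0.0450/0.0431 = 1.04; Φ(1.04 − 1.96) ≈ 0.18.

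Two cross-checks agree. The logistic approximation gives √(175 × 0.44 × 0.56 × 0.32) × ln 1.42 = 1.30, hence about 0.255 at D' = 1. A 10,000-run simulation of the trend test gives 27% and 18%.

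**Step 4, attempts to reach the stated 80%.**

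| Variant | D' = 1 | D' = 0.8 |
|---|---|---|
| OR 1.42, N = 175, allelic, two-sided | 26% | 18% |
| same, one-sided | 37% | 28% |
| dominant carrier test, two-sided | 20% | 14% |
| 2-df test, log-additive / dominant effect | 20% / 15% | 14% / 11% |
| OR 1.42, N = 350 (154 v 196), or 175 + 175, two-sided | 46% | 32% |
| 1.42 as relative risk, N = 175, two-sided | 73% | 54% |
| 1.42 as relative risk, N = 350, two-sided | 95% | 83% |

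Keeping 1.42 as an odds ratio, even 350 people combined with a one-sided test reach only 58% at D' = 1. With the Protocol's D' of 0.8, a value near 80% appears only when 1.42 is read as a relative risk and about 350 people are assumed (83% for multiplicative risks, 77% for additive). At prevalence 0.44 a relative risk of 1.42 is an odds ratio of about 1.90 for one copy against none.

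**Step 5, what 175 patients can detect.** For 80% power the observed z must average about 1.96 + 0.84 = 2.80.
- D' = 1: at OR 2.17 the allele frequencies are 0.268 and 0.147, difference 0.1215, z = 2.82, power 80%.
- D' = 0.8: at OR 2.68 the difference is 0.8 × 0.1515 = 0.1212, z = 2.81, power 80%.

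A dominant carrier test would need 2.44 or 3.16.

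**Step 6, N for OR 1.42.** (1.96 + 0.84)² / (0.44 × 0.56 × 0.32 × 0.3507²) ≈ 810 at D' = 1. Dividing by 0.8² gives about 1,265 at D' = 0.8.

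**Step 7, the full breast cohort.** Sections 5.1 and 7.1 give 2,100 × 0.75 = 1,575 patients with 2-year data, that is 693 with pain and 882 without if prevalence is the same. SE = 0.0144, so z = 3.92 (D' = 1) or 3.13 (D' = 0.8), and power at alpha 0.05 is 97% or 88%. At the main study's alpha of 5 × 10⁻⁵ (critical value 4.06) it falls to Φ(3.92 − 4.06) ≈ 44% or Φ(3.13 − 4.06) ≈ 18%. At that alpha, 175 patients have less than 0.5%.

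**The case against.** The best defence is that the sample size was never derived from this calculation. It follows from a 50% return rate at one centre, genotyping is only one part of a questionnaire sub-study, and correcting the figure changes neither recruitment nor any main-study endpoint. That stands and limits the consequence, but it does not make the number right. All numerical inputs are printed in the same sentence, so this is not detail left for an analysis plan.

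A second defence is that the model and sidedness are unstated, so the claim may rest on other choices. The table covers those choices, and none that keeps 1.42 as an odds ratio gets there. With 175 patients, 80% is passed (82%) only if 1.42 is a relative risk, D' is dropped and the test is one-sided, which is not what is written.

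Three further readings are tempting, and the documents do not support them:

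- *The SNP findings would be mostly false.* A reader might infer this from alpha 0.05 beside whole-genome data. The Protocol does not say that every SNP will be tested at 0.05. Section 7.2 names Bonferroni correction and Section 7.1 uses 5 × 10⁻⁵ for 1,000 SNPs. What can be said is that the power figure applies to one SNP only.
- *The genetic analysis belongs in the whole breast cohort.* Genome-wide typing there is only described as possibly feasible (Section 6.6.1), and the pain-sensitivity data exist only for the subset. A whole-cohort analysis is supported for the selected markers and the main-study pain outcome, as an addition.
- *The detectable odds ratio is about 2.0 (D' = 1) or 2.3 (D' 0.8).* That follows if the 0.2 is placed in pain-free patients, which also lifts power at 1.42 to 28% and 20%. In a cohort where 44% have the outcome, 0.2 is more naturally the frequency in everyone; then odds ratios of 2.0 and 2.3 have only about 72% and 67% power.

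**Conclusion.** The stated 80% is wrong as written. From the Protocol's own inputs, power for an odds ratio of 1.42 is about 18% at D' 0.8 and 26% at D' = 1, so the claim is roughly three to four times too high. The result assumes a two-sided allelic or log-additive test, an allele frequency of 0.2 across the cohort, and a marker of the same frequency. The other tests tried (dominant carrier, 2-df) give less; a one-sided test gives at most 37%.

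A mix-up of relative risk with odds ratio, together with the 350 invited patients instead of the 175 expected, would produce a figure near 80%. That origin is a guess; the text does not state it. The error affects how the sub-study's genetic results may be read, and nothing in the main study.

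**What to change.** Replace the power sentence in Section 16.1 with one along these lines: 175 patients (about 77 with pain) give 80% power at two-sided alpha 0.05 to detect a per-allele odds ratio of about 2.2 if the typed SNP is the causal one, or about 2.7 at D' 0.8, for a single pre-named SNP with allele frequency 0.2 and a marker of the same frequency. State the genetic model, sidedness and marker frequency that the sponsor actually intends, and recompute if they differ. If 1.42 was meant as a relative risk, say so and give the power for 175 patients (54% at D' 0.8).

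Add to Section 16.3.3 that this figure does not apply to the whole-genome SNP data and that whole-genome results in the subset are exploratory.

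Optionally, test the selected markers against 2-year breast pain in the roughly 1,575 evaluable breast patients. C30 and BR23 are scheduled at 24 months for all of them (Section 12.1), all give DNA (Section 6.2), and all are typed for the selected markers (Section 6.6.1). Set the alpha to the number of markers tested. Keep the 175-patient subset for analyses that need the added pain questionnaires.

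The cost is a less favourable stated power and, if the option is taken, one further analysis without adjustment for pain sensitivity. No extra patients or samples are needed.

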## 16.2 Background

### 16.2.1 Chronic breast-pain following breast cancer treatment

Breast cancer is the most frequently diagnosed cancer in women^69^. The prevalence of chronic pain in breast cancer patients ranges from 25-60% within different populations, but it tends to be underreported by survivors^69^. Research has shown that chronic pain has an association with reduction in quality of life, affecting work re-entry, productivity and an individual’s identity^71,72^

Patients regard the risk of long-term breast pain as an important factor in treatment decision-making^73^. Owing to improvements in diagnosis and treatment, there are an increasing number of long-term breast cancer survivors living with late side-effects of treatment such as chronic breast-pain^71,74^. The causes associated with certain types of pain after breast cancer treatment have been clearly identified, for example, peripheral neuropathy associated with chemotherapy, or bone pain with aromatase inhibitors^75,76^. However, the underlying causes and mechanism of long-term breast pain in breast cancer survivors remain unclear.

Studies of breast cancer survivors have shown that chronic breast pain generally resolves with time^72,77,78^. Nevertheless, these studies have not considered other factors, such as ethnicity and age. In terms of ethnicity, studies in different clinical chronic-pain conditions have shown that pain perception can vary owing to differences in sociocultural and neurobiological processes^79-84^. In older patients, the increased incidence in chronic breast pain has been attributed to the more aggressive nature of cancer, use of chemotherapy and links to anxiety and depression^85,86^. Our understanding of the interaction between the protective effect of time and other patient clinical or biological factors is limited.

Pain perception is subjective, with many neurocognitive aspects modulating the end pain experience87. Anxiety has been linked with the emotional response to pain, however, the exact effect of anxiety on pain perception remains ambiguous^88-90^. Within breast cancer survivors, patients with anxiety and depression are more likely to report long-term pain post-breast cancer treatment with a higher percentage being younger women^70,91,92^.

